### Procedures

At the enrollment phase, families will be screened for inclusion criteria in a telephone interview (see Fig. 1). If the study requirements are met, the adolescents and their caregivers will be informed about the study procedures during an initial contact meeting and will receive the consent form. External randomization will be performed by a researcher who is not involved in the study. All patients will undergo an initial clinical assessment to determine clinical parameters (e.g., weight, height, BMI, pulse). The therapists will discuss the initial FBT-interventions with the family and, after randomization, inform the family whether they will additionally receive guidance for FBT-HT or FBT-MBSR. After the initial interview, both the adolescents and their parents will receive a web-based link to an electronic test battery assessing psychopathology and interfamily relationships to be completed within 7 days. The study intervention will last 3 months. At the end of the treatment phase, the clinical staff will again collect clinical parameters, and another link to an electronic test battery will be sent. During the 3-month treatment phase, weight, blood pressure, and pulse will be recorded weekly. In addition, treatment progress is to be assessed by both patients and therapists after each FBT consultation. After 12 months, families will be contacted by email and asked to complete the final test battery.

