The purpose of the proposed study (randomized clinical trial) is to compare the three outpatient treatments (FBT, FBT-HT, FBT-MBSR) for adolescents with AN. We hypothesize that FBT-HT is acceptable, appropriate and feasible and, importantly, outperforms both established FBT alone and FBT supplemented with mindfulness-based stress reduction training (FBT-MBSR) in terms of adolescent weight gain and eating disorder psychopathology. Our primary endpoint is remission of AN symptoms, defined as an increase in body weight as measured by BMI, and a decrease in eating disorder pathology as measured by the Eating Disorder Examination (EDE) total score and EDI-2 total score. Secondary endpoints include stabilization of somatic health status, as measured by vital signs, as well as an improvement in psychosocial well-being and reduction in perceived stress. We hypothesize that FBT-HT will lead to stress reduction in caregivers as well as improvement in interfamily relationships and regulation of perceived and expressed emotions within the family. In addition, we expect that balanced and relaxed family dynamics (integrated in further exploratory analyses as a mediator/moderator variable) will lead to increased effectiveness of FBT and thus improved patient-related outcomes.

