#### Interfamily relations as mediator/moderator

In order to examine how perceived intrafamily stress affects different treatment schemes, at the beginning of treatment and at follow-up assessments, both adolescents and parents are to be interviewed using the short version of the Family Questionnaire (FB-K; German translation, Familienbogen–Kurzversion; [4], a self-report instrument used to assess family function in relation to two aspects: (1) emotional connection between family members and (2) willingness to communicate.

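### Nothing requires the week-0 online questionnaires, including EDE and EDI-2, to be completed before families learn their arm, so the pre-test of two primary outcomes is not protected from knowledge of allocation

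*Protocol article*

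**What the plan says.** Procedures first names the allocation step: "External randomization will be performed by a researcher who is not involved in the study". A clinical assessment follows: "All patients will undergo an initial clinical assessment to determine clinical parameters (e.g., weight, height, BMI, pulse". Next comes the therapist meeting: "The therapists will discuss the initial FBT-interventions with the family and, after randomization, inform the family whether they will additionally receive guidance" for one of the two add-on arms. The next sentence begins "After the initial interview, both the adolescents and their parents will receive a web-based link to an electronic test battery" and describes an "electronic test battery assessing psychopathology and interfamily relationships to be completed within 7 days". The next battery mentioned is the one at the end of treatment, so this one supplies week 0.

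Table 1 (Measures) marks EDE and EDI-2 as adolescent online self-report, with values at week 0, week 12 and 12 months. KIDSCREEN-27, BDSEE, PSS-10, FB-K and CBCL are also answered online by adolescents or caregivers and also have a week-0 value. The Introduction makes the two eating-disorder scores part of the primary endpoint: "a decrease in eating disorder pathology as measured by the Eating Disorder Examination (EDE) total score and EDI-2 total score", alongside BMI. For FB-K, the section on interfamily relations says that "at the beginning of treatment and at follow-up assessments, both adolescents and parents are to be interviewed".

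The Data analysis plan assesses the interventions as change in EDE, EDI-2 and BMI from pre-test, using repeated measures ANOVA and then Tukey's test when there is a significant effect.

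**The concern.** Read in order, the text has the family hear its allocation and then answer the questionnaires that serve as its baseline. An adolescent or parent who has just learned that they will, or will not, receive home visits may rate symptoms, stress or family climate differently for that reason.

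Pre-test is one level of the repeated measure. A baseline shift in one arm that does not persist to the same extent at week 12 therefore appears as a difference in change between arms. It could favour any arm, and the data could not separate it from a treatment effect.

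Two further uses of the questionnaire baselines are weakened. Baseline comparisons made to judge the randomisation are hard to read for values given after disclosure. So is FB-K as a moderator, if allocation may already have altered it.

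Follow-up self-reports in a trial like this cannot be blinded. The baseline self-report can be fully protected, and cheaply.

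**Working it through.** **1. Order of events.** Two readings of the initial interview are possible.
- It is the therapist meeting just described. The battery is then sent after disclosure of the arm and after a first FBT discussion.
- It is an earlier contact. The link may then go out before disclosure, but the 7-day window is not required to close before randomisation, disclosure or the first session.

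On neither reading is a pre-disclosure baseline assured. Weight, height and BMI come from the clinical assessment and do not depend on this.

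**2. The plan's own sample size, reproduced.** Inputs from Power analysis: f = 0.2, power 80%, alpha 0.05, r = 0.5, three groups, two time points, N = 66, 25% attrition, target 90.
- Noncentrality: λ = f²·N·m/(1−r) = 0.04 × 66 × 2/0.5 = 10.56, with 2 and 63 df.
- Power is 0.818 at N = 66 and 0.798 at N = 63, so 66 is the smallest total with equal arms.
- 66/0.75 = 88, rounded up to 90.

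These figures stand.

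**3. The planned effect on the change scale.**
- SD of change = σ√(2(1−r)) = σ√(2 × 0.5) = σ.
- f for change = √(λ/N) = √(10.56/66) = 0.40.
- If one arm differs by D from two equal arms, the SD of the three means is D√2/3, so D = 0.40 × 3/√2 = 0.85 SD.
- If the arms are equally spaced, the outer two differ by 0.98 SD.

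**4. Illustrative bias.** The documents give no disclosure effect. Assume that knowing the arm moves one arm's baseline by s SD and that a fraction p of this is still present at week 12. The change contrast is then biased by s(1−p). With no true effect and N = 66, λ = 66 × (2/9) × [s(1−p)]².

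| s (SD) | share of 0.85 SD (p = 0) | omnibus false positive, p = 0 | omnibus false positive, p = 0.5 |
|---|---|---|---|
| 0 | 0% | 5.0% | 5.0% |
| 0.1 | 12% | 6.1% | 5.3% |
| 0.2 | 24% | 9.5% | 6.1% |
| 0.3 | 35% | 15.6% | 7.4% |

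With p = 1 the shift cancels and the rate stays at 5%.

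**5. Pairwise result under the plan's procedure.** For the affected pair, Tukey's test is run only after a significant interaction. Simulation (22 per arm, p = 0) gives about 1.8% with no shift and 2.4%, 4.4% and 8.2% for shifts of 0.1, 0.2 and 0.3 SD.

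**6. Power.** If a shift with p = 0 works against a true 0.85 SD difference, power falls from 0.82 to 0.71, 0.57 or 0.43. If it works with it, power rises to 0.90, 0.95 or 0.98.

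**The case against.** The best defence is that the text is loose rather than wrong. The same paragraph mentions a telephone interview, an initial contact meeting and an initial clinical assessment, and it never calls the therapist discussion an interview. It is not strictly chronological either: randomisation is named before the clinical assessment and again afterwards. Fig. 1, the schedule of procedures, is not shown and might settle the order. This stands as far as certainty goes. A reader might infer that all baseline questionnaires are definitely answered by people who know their arm; the article does not establish that. It does establish that nothing prevents it.

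A reader might also infer that any baseline shift passes in full into the treatment contrast. That needs the shift to be gone by week 12. Families know their arm at both times, and a reporting tendency that persists cancels in the change score, as the p = 0.5 column shows in part.

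Third, a reader might count the first week of treatment as bias. The opening FBT discussion and the weekly FBT sessions are common to all three arms, so that exposure is largely non-differential, and no passage says that add-on visits take place before the battery is answered.

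Fourth, quoting an unadjusted pairwise t-test would overstate the error rate. At 0.3 SD it gives about 17%, against 8.2% under the plan's gated Tukey procedure.

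Finally, the scope is limited. BMI is untouched, the planned confounders are largely historical facts, and the FB-K analysis is exploratory.

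**Conclusion.** The point holds as a defect of sequence. As written, the pre-test of EDE and EDI-2 is not secured before the arm is known, and the primary analysis depends on that pre-test.

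Neither the direction nor the size of any bias can be derived from the documents. The rise in the omnibus false-positive rate from 5% to about 6%, 9% or 16% is an illustration. It assumes a shift of 0.1, 0.2 or 0.3 SD confined to one arm and gone by week 12, 22 per arm and r = 0.5. Expressing the shift as 12%, 24% or 35% of the planned effect also assumes that one arm differs from two equal arms. The sample size is not in question.

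It should be fixed. Confidence is medium to high: high that no safeguard is stated, lower that the battery in fact follows disclosure in every family.

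**What to change.** - Define the initial interview in Procedures. State that the week-0 battery, adolescent and caregiver, is completed after consent and before the allocation is released to the family.
- Enforce this with a completion check in REDCap, which already delivers the instruments, and keep the 7-day limit.
- State a rule for families who do not finish in time. For example, release the allocation at day 7, flag the baseline as missing or post-disclosure, and keep the family in the analysis as randomised.
- For families already enrolled, record the battery's completion date relative to disclosure. Add a sensitivity analysis that sets post-disclosure EDE and EDI-2 baselines to missing under the planned maximum likelihood handling. If most baselines are post-disclosure, compare the arms on week-12 scores alone. At r = 0.5 this loses no precision, because the change score has variance 2(1−0.5)σ² = σ², the same as a single score.

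**Cost:** protocol wording, a REDCap check and one date field. Allocation may be delayed by up to 7 days. No assessment is added and the sample size does not change.

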#### Effectiveness

Adolescents’ heights and weights are to be measured to determine BMI at all follow-up timepoints along with an assessment of eating disorder symptoms using the EDE and the Eating Disorder Inventory (EDI-2; [34]). Both instruments have excellent reliability and validity [7, 12]. The primary outcomes for adolescents are improvement in BMI *z*-score based on the CDC growth charts, as well as a decrease in eating-related psychopathology. Secondary endpoints include stabilization of somatic health status, as measured by vital signs (blood pressure and pulse), improvement in psychosocial well-being and reduction in perceived stress. Accordingly, parents will complete the Perceived Stress Scale (PSS; [5]), which is commonly used to quantify subjective feelings of stress. Adolescents will also complete the Brief Dyadic Scale of Expressed Emotion (BDSEE; German translation by [32]), which captures expressed emotions from the patient’s perspective.

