### Power analysis

The target sample size for the primary analysis was derived from an a priori power calculation using G*Power (version 3.1.9.7) and repeated measures ANOVA as a statistical model. Assuming a small effect size of *f* = 0.2, power of 80%, type 1 error level of *p* < 0.05 and correlation among repeated measures of *r* = 0.5, the necessary total sample size of 66 is adequate to test our main hypothesis involving three groups, two time points and the statistical interaction term. Assuming a reasonable attrition rate of 25%, we set our target sample to 90, equivalent to 30 participants per group, assuming equal treatment arm sizes. This number also aligns with the study feasibility, as it approximates the number of eligible patients who previously registered at the outpatient clinic over time intervals similar to the planned recruitment period of 3 years.

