### Data analysis plan

The initial descriptive statistics will summarize participant data characteristics as means, standard deviations, minima, maxima, frequencies and percentages. The validity of stratified randomization will be evaluated by inspecting between-group differences at baseline by means of a one-way analysis of variance (ANOVA), Kruskall–Wallis test or chi-squared test (in dependency of conventional statistical assumptions and the variable type, i.e., continuous versus categorical). Outcome data will be evaluated for the normality assumption by a combination of visual (Q–Q plots, histograms) and statistical (Shapiro–Wilk test) methods and will be transformed if necessary to meet the normality assumption. Participant characteristics of the analyzed sample and dropouts will be subjected to an additional inspection for possible non-random differences. Missing data will be handled by the maximum likelihood estimation method. The effects of the interventions will be assessed as changes in the primary outcomes from pre-test to post-test and follow-up assessment using EDE, EDI-2 and BMI analyzed with a repeated measures ANOVA followed by a post-hoc Tukey’s test to compare treatment means when there is a significant effect. The potential influence of confounding factors (age, premorbid BMI, duration of illness, age at onset, duration and setting of pre-treatment, medication use) will be further explored in sensitivity analyses. The secondary continuous variables will be analyzed in parallel. The measures related to treatment implementation (FBB, BPT) will be evaluated using descriptive statistics. Corrected effect sizes, expressed as Hedges’s *g* and significant deviations beyond the 95% confidence interval, will be computed for between- and within-group terms and will indicate empirical power estimates for a subsequent confirmatory study. Exploratory analyses will test the FB-K measure as a mediator/moderator of efficacy. To examine the FBT process, the ratings of each therapy session by the adolescents and the therapists will be compared and analyzed to assess their common development over time. More advanced statistical methods, such as generalized estimating equations (GEE) (which allow for more flexible modelling of the correlation structure among observations, are less sensitive to violation of assumptions and estimate population-wide average effects) will be also applied to assess differences in BMI percentiles and EDE/EDI-2 trajectories. The statistical significance threshold will be set to *p* < 0.05.

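### Weight is recorded weekly during treatment, but the stated primary BMI analysis uses only week 0, week 12 and 12 months, so early leavers contribute baseline BMI alone

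*Protocol article*

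**What the plan says.** The Procedures section sets the collection: "During the 3-month treatment phase, weight, blood pressure, and pulse will be recorded weekly". This applies to all arms.

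The Effectiveness section names the variable, "The primary outcomes for adolescents are improvement in BMI *z*-score based on the CDC growth charts", and its timing: "heights and weights are to be measured to determine BMI at all follow-up timepoints". Table 1 marks BMI at week 0, week 12 and 12 months. The table does have a weekly entry, but uses it only for the post-session report (BPT).

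The Data analysis plan fixes the primary analysis of effects: "assessed as changes in the primary outcomes from pre-test to post-test and follow-up assessment using EDE, EDI-2 and BMI analyzed with a repeated measures ANOVA". On incomplete data it says: "Missing data will be handled by the maximum likelihood estimation method". On dropouts it says: "Participant characteristics of the analyzed sample and dropouts will be subjected to an additional inspection for possible non-random differences". Generalised estimating equations "will be also applied to assess differences in BMI percentiles and EDE/EDI-2 trajectories"; this is an addition, and its time points are not given.

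The Power analysis section anticipates the loss: "Assuming a reasonable attrition rate of 25%, we set our target sample to 90". No section assigns the weekly weights to an analysis.

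**The concern.** Maximum likelihood corrects for dropout only through the data in the model. With the scheduled waves alone, a patient who stops in week 7 supplies a baseline BMI and nothing on progress since, although several weights taken during treatment exist. The model then predicts that patient's week-12 value from patients with a similar baseline who stayed.

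The trial's hypothesis is that FBT-HT gives better weight gain, and poor gain is a plausible reason for leaving outpatient treatment. If the two are linked, a likelihood analysis of weeks 0 and 12 is not protected, while one that includes the weekly values can be. This is separate from the choice between ANOVA and a likelihood model: what is missing is the data, not the estimator.

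**Working it through.** **1. The plan's own figures.** Inputs from the Power analysis section: f = 0.2, r = 0.5, k = 3 groups, m = 2 time points, alpha 0.05. For the group-by-time interaction:

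- lambda = f² × N × m / (1 − r) = 0.04 × 66 × 2 / 0.5 = 10.56
- degrees of freedom (k − 1)(m − 1) = 2 and (N − k)(m − 1) = 63
- power = 0.818; with N = 63 it is 0.798

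So 66 reproduces as the smallest total with equal arms. Attrition: 66 / 0.75 = 88, rounded up to 90. At 25%, 90 × 0.25 = 22.5, so about 22 patients may lack a later value. The sample size is not in question.

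**2. Bias at week 12, one dropout mechanism for all arms.** From the article: r = 0.5 (used between weeks 0 and 12) and 25% attrition. Assumed: SD 1, exponentially decaying correlation, 3% measurement error, true FBT-HT advantage 0.60 SD, all attrition before week 12 and driven by weight change at week 6. With 400,000 simulated patients per arm:

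| Who leaves | Likelihood, weeks 0 and 12 only | Shortfall |
|---|---|---|
| Odds ratio 1.5 per SD of poor change | 0.596 | 1% |
| Odds ratio 2 | 0.588 | 2% |
| Odds ratio 3 | 0.575 | 4% |
| Everyone below a fixed cutoff, nobody else | 0.51 | 15% |

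Under the cutoff, dropout is 31% in control and 19% in FBT-HT, completers alone give 0.49, and likelihood with the weekly weights gives 0.60. If only half of the attrition falls before week 12, the cutoff gives 0.543 (about 10% low) and odds ratio 3 gives 0.586 (about 2% low). With a true difference of 0, the bias is 0.

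**3. A second set of assumptions, including mechanisms that differ by arm.** Assumed: baseline SD 0.8 BMI-z, mean slope 0.03 per week, slope SD 0.04, residual SD 0.12, and 22-31% dropout before week 12. Where dropout is weight-driven, the chance of leaving is renewed each week from the observed change.

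| Mechanism | True | Weeks 0 and 12 only | With weekly values |
|---|---|---|---|
| Same in both arms, no effect | 0 | about 0 | about 0 |
| Same in both arms, real effect | 0.24 | 0.19 | 0.235 |
| Poor gainers leave one arm, random in the other | 0 | −0.15 | about 0 |
| Opposite in the two arms | 0 | −0.30 | about 0 |

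The second row is about 20% low (0.05 / 0.24), so the 15% above is not an upper bound. The last two rows show a difference arising where none exists; exchanging the arms reverses its sign. With weekly values the error is within Monte Carlo error in all four rows, because dropout here depends only on observed weights.

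**4. Precision when dropout is unrelated to weight.** With 30 per arm and 25% dropout spread over the 12 weeks, the variance of the week-12 contrast with weekly values is 0.85-0.93 of that from two-wave likelihood, a cut of 7-15%. The exponential-decay cases give 7-8%; the upper end needs other assumed covariances, such as random slopes. The standard error shrinks by 1 − √0.93 = 4% to 1 − √0.85 = 8%.

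**5. Scale.** With r = 0.5 the SD of change is √(2 × (1 − 0.5)) = 1, so with about 22 completers per arm the standard error is √(2/22) = 0.30 SD. The cutoff's shortfall of 0.09 is 0.3 standard errors; the 0.004-0.025 under odds ratios 1.5-3 is below 0.1.

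**The case against.** The best defence is that the article is condensed. The maximum likelihood sentence does not list the variables in the model, the GEE sentence gives no time points, and a full analysis plan may bring the weekly weights in. A reader might infer that the trial throws these weights away. The documents do not show that; they show only that no stated analysis uses them. But the article does fix the model and the waves for the primary outcome, and that choice can be questioned as written. The GEE analysis does not settle it: it is supplementary, and ordinary unweighted GEE generally needs data missing completely at random.

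A reader might also infer a material bias toward no difference. That is not supported. The 15% figure needs a deterministic cutoff and all attrition before week 12. The article does not divide its 25% between the treatment phase and the 12-month contact, which is by email, so later loss is plausible. Nor does it say that someone who stops therapy cannot be weighed at week 12. The direction toward no difference requires one mechanism across arms and a real effect.

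Two further points stand. EDE and EDI-2, the other primary measures, gain nothing. And the remedy is not free: 13 weekly points in three arms give 39 means, and an unstructured covariance adds 13 × 14 / 2 = 91 parameters with 90 patients.

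**Conclusion.** The point holds as a cheap improvement to the stated primary BMI analysis, not as an error that invalidates it. As written, a patient lost before week 12 contributes only baseline BMI, and maximum likelihood cannot use the weight course that the trial records.

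With a true advantage of 0.60 SD, all 25% attrition before week 12 and a shared mechanism, the shortfall is about 1-4% for odds ratios of 1.5-3 and about 15% under a cutoff. It is smaller if some attrition comes later, and zero if dropout is unrelated to weight or if a shared mechanism meets no true effect. If mechanisms differ by arm, it can take either sign and reach 0.15-0.30 BMI-z under the assumptions in step 3. Including the weekly values removes it where dropout depends on recorded weight, and otherwise still cuts the variance by roughly 7-15%. None of the dropout mechanisms is stated in the article.

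**What to change.** In the Data analysis plan, do one of the following:

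- **Preferred:** analyse BMI z-score with a likelihood-based mixed model that includes the weekly values (weekly weight with the nearest measured height) together with the 12-month value. Prespecify a structured covariance and estimate the arm contrasts at week 12 and at 12 months.
- **Alternative:** keep the three scheduled waves and enter the weekly weights as auxiliary variables in the missing-data model.

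Add weekly weight to Table 1 so that it agrees with the Procedures section. EDE and EDI-2 are unchanged.

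This needs no new visits, measurements or patients. It costs the export of the weekly weights to the study database and the choice of a covariance structure that 90 patients can support. A misspecified structure could bring back some bias, so a sensitivity check with a second structure should be prespecified. Carrying height from a measured visit is a small approximation over 12 weeks. The change adds little for patients lost between week 12 and 12 months.
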